## Methods

### Patient and public involvement

Patients or members of the public were not actively involved in designing this trial. However, feedback from patient support groups such as Long COVID Austria and ME/CFS Austria helped inform the recruitment strategy. Additionally, a qualitative substudy is planned to collect systematic feedback from involved patients regarding their experiences with the intervention and the trial procedures. This input will be considered when interpreting results and shaping the dissemination strategy.

### Trial design

This study is an ongoing single-centre, partially blinded, 12-week RCT with a sham control conducted at the Medical University of Vienna. Participant enrolment began on 19 March 2026. This protocol was developed in accordance with the Standard Protocol Items: Recommendations for Interventional Trials (SPIRIT) guidelines. The study is registered at ClinicalTrials.gov (Identifier: NCT06996314) and will be reported according to the Consolidated Standards of Reporting Trials (CONSORT) statement.^26^

Participants will be randomised using stratified block randomisation in a 1:1:1:1 ratio to one of four groups:

AVNT+SDBAVNT+NBSham AVNT+SDBSham AVNT+NB

The randomisation will be based on the presence or absence of post-exertional malaise (PEM) (yes/no).

### Trial setting

The trial will be conducted at the Medical University of Vienna, in cooperation with the second Department of Medicine with Cardiology and Intensive Care Medicine in a specialised autonomic laboratory.

### Eligibility criteria

#### Inclusion criteria

Age between 18 and 65 years.Formal POTS diagnosis confirmed by current consensus criteria: sustained HR increase of at least 30 bpm within 10 min of standing (head-up tilt test (HUTT), 70°), in the absence of orthostatic hypotension (SBP fall ≥20 mm Hg or diastolic BP fall ≥10 mm Hg), with characteristic symptoms persisting for at least 6 months.^27^Participants with Long COVID will be included if they meet the formal diagnostic criteria for POTS. Among those experiencing PEM, only individuals who have been clinically stable for more than 2 months, exhibit mild PEM and regularly employ pacing strategies will be eligible.Participants on POTS medication must be on stable dosing for at least 4 weeks prior to enrolment. Medication will be continued throughout the study, and participants will be grouped by medication class for subgroup analysis. Any changes in medication during the study must be reported immediately and documented for analysis.Participants must be able and willing to provide written informed consent.Sufficient German or English language proficiency to complete questionnaires and provide informed consent.

#### Screening of participants without a prior diagnosis

Individuals without a prior formal POTS diagnosis but who report characteristic symptoms for at least 6 months (eg, dizziness, chronic fatigue, syncope, brain fog, palpitations, exercise intolerance) will undergo a standardised HUTT (70°) at the study site in order to establish a formal diagnosis according to current consensus criteria.

HR and BP will be recorded during a supine rest period and during head-up tilt. The orthostatic HR response is assessed as the change in HR from supine to upright position (ΔHR) within the first 10 min of tilt.A ΔHR of ≥30 bpm within 10 min of head-up tilt (70°), in the absence of orthostatic hypotension (SBP fall ≥20 mm Hg or diastolic BP fall ≥10 mm Hg), fulfils the diagnostic criteria for POTS; in participants with a ΔHR of 25–29 bpm, the diagnostic criteria are likewise considered fulfilled if typical orthostatic symptoms are present and clinical judgement supports the diagnosis.

Participants who do not meet the diagnostic criteria will not be enrolled.

#### Exclusion criteria

Participants meeting any of the following criteria will be excluded from the study:

Significant hypertension, either in the supine or standing position, defined as BP readings exceeding 150 mm Hg SBP or 100 mm Hg DBP.Orthostatic hypotension, defined as a consistent BP decrease of >20 mm Hg SBP or >10 mm Hg DBP within 10 min of standing.Cardiac rhythm or conduction disorders that may interfere with autonomic assessment, including atrial fibrillation (paroxysmal, persistent or permanent), presence of a pacemaker or an implanted cardioverter defibrillator.Recent stroke or myocardial infarction within the past 6 months.History or presence of significant systemic diseases, including malignancies, autoimmune disorders, clinically relevant immunological or haematological diseases or severe anaemia (haematocrit <28%).Neurological conditions that may confound autonomic or cardiovascular measurements, including seizure disorders, Menière’s disease or a surgically severed vagus nerve (eg, prior vagotomy).Orthopaedic, rheumatological or postoperative conditions that limit safe participation in HUTT.Current pregnancy or lactation.Ear-related contraindications to auricular stimulation, including cochlear implants, history of ear surgery, recent ear injuries or infections, or negative prior experiences with electrotherapy.Acute illness, including fever at the time of assessment.Current psychiatric disorders that, in the judgement of the investigators, may interfere with study participation or adherence.Inability or unwillingness to provide written informed consent.

Insufficient German or English language proficiency to understand study procedures, provide informed consent, or complete study questionnaires.

### Eligibility criteria for sites and individuals

Since this is a single-centre trial conducted at the Medical University of Vienna, no additional site-specific eligibility criteria are necessary. The trial will take place in the autonomic laboratory of the second Department of Medicine with Cardiology and Intensive Care Medicine at Clinic Landstrasse. Assessments, including physiological testing and data collection, will be performed by a trained study nurse with expertise in autonomic and cardiovascular assessments. The breathing therapy intervention will be administered by a licensed physiotherapist with over ten years of experience in respiratory and autonomic rehabilitation.

### Intervention and comparator

Before starting the intervention, all participants attend a 60-minute introductory training session led by a physiotherapist experienced in respiratory and autonomic therapy, where the correct use of the device, electrode placement and adherence strategies are covered. The first stimulation session is carried out under supervision to ensure proper application and participant safety.

#### Auricular vagal neuromodulation therapy

AVNT will be administered using the Nurosym device (Parasym Health, London, UK), a CE-certified and clinically validated medical device. Stimulation is applied via ear electrodes placed at the cymba conchae of the left ear; an anatomical site innervated by the auricular branch of the vagus nerve. The device settings are uniformly applied to all participants according to established clinical standards and in accordance with the study by Stavrakis *et al*.^20^ Specifically, stimulation is administered with a pulse frequency of 20 Hz and a pulse width of 200 microseconds. The intensity is individually adjusted for each participant to evoke a noticeable but comfortable tingling sensation without causing pain or discomfort. Each participant undergoes one stimulation session daily, lasting 60 min, over a total intervention period of 12 weeks.

#### Sham stimulation

Participants in the sham groups use the same device with the same electrode placement. However, the sham device does not deliver electrical current. Instead, a sound-sham method is used, in which the device emits pulsed acoustic signals that mimic the auditory cues of active AVNT but have no physiological effect on vagal pathways. This method provides a high-quality placebo control and preserves participant blinding.

#### Diaphragmatic breathing

Diaphragmatic breathing therapy will be carried out according to a standardised protocol with individual adjustments based on baseline assessment using the Breathing Pattern Assessment Tool (BPAT). This will enable differentiation between restrictive and functional breathing disorders. Resting respiratory rate will also be documented to establish individual baseline values and guide therapy progression.

The technique involves nasal inhalation with controlled abdominal expansion followed by passive exhalation through lightly pursed lips. When needed, segmented inhalations and brief inspiratory pauses will be included to improve tidal volume control and muscle coordination. Therapy will progress gradually, with the respiratory rate decreased by about 20%–30% relative to baseline during the initial phase (aiming for 10–11 breaths/min in weeks 1–2; 8–9 breaths/min in weeks 3–4). From week 4 onwards, participants will switch to a slow-breathing protocol of 4 s inhalation, 6 s exhalation and a 2–3 s postexhalation pause, targeting roughly 5 breaths/min.

Breathing therapy will be supported by a mobile application that provides visual or acoustic pacing cues and records practice frequency. The planned therapy duration will be at least 10 min daily during weeks 1–4 and at least 15 min per day from week five onwards. Safety monitoring will require immediate cessation of the exercise and notification of the study team in cases of dizziness, paraesthesia, thoracic discomfort or presyncope. Participants will submit a weekly breath training diary via the breathing app to allow monitoring of adherence to the breathing intervention.

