### Objectives

The main aim is to assess whether 12 weeks of AVNT combined with SDB (AVNT+SDB) produces a greater improvement in autonomic function, measured as a reduction in the orthostatic HR change (ΔHR) during a standardised 70° head-up tilt, than AVNT+NB, sham AVNT+SDB or sham AVNT+NB. ΔHR is predefined as the mean HR during the 10-minute upright head-up tilt phase minus the mean HR during the 10-minute supine baseline period; comparisons between AVNT+SDB and each other group are confirmatory, while all other pairwise comparisons are exploratory.

Secondary objectives include characterising between-group differences in beat-to-beat BP responses (mean arterial pressure (ΔMAP), systolic BP (ΔSBP), diastolic BP (ΔDBP), the initial orthostatic nadir, and time to recovery). Respiratory sinus arrhythmia (RSA) is assessed as an index of cardiac vagal modulation using ECG-derived HR variability (HRV), assessing patient-reported outcomes using the Short Form Health Survey (SF-36) for health-related quality of life, the Hospital Anxiety and Depression Scale (HADS) for symptoms of anxiety and depression, Chalder Fatigue Scale (CFS), the Malmö POTS Symptom Score (MAPS) and the Nijmegen Questionnaire (NQ) for symptoms of dysfunctional breathing.

As a safety objective, the trial will evaluate tolerability and systematically record adverse events (AEs) and serious AEs (SAEs), including treatment-related discontinuations, throughout the study, with descriptive comparisons of event profiles across the four groups.

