AEs: Participants will be encouraged to report any new or unusual symptoms to the study team promptly. This could be done via phone, email or during routine check-ins. These events, regardless of whether or not they are related to the study, will be recorded and monitored by the team. Discontinuation due to AEs: If a participant chooses to discontinue the intervention due to a perceived decline in health or adverse reactions, this will be documented and analysed. To ensure accurate and consistent data, participants might be asked to complete a simple AE questionnaire on a weekly basis. This could be administered as an online survey or over the phone, depending on the participant’s preference. If any severe or concerning symptoms arise, participants will be instructed to contact the study team immediately. All collected data will be systematically recorded and evaluated to monitor the safety of the intervention.

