### Harms

Harms are defined as any AEs or side effects occurring during the trial, regardless of their causal link to the intervention. They will be assessed systematically through weekly AE questionnaires, supplemented by spontaneous reports from participants via phone, email or during visits. All events will be recorded in the case report form, including their severity, onset and duration. Discontinuation owing to AEs is permitted at any time, and reasons will be documented. Severe or concerning symptoms will prompt immediate contact with the study team. This structured monitoring ensures that both subjective complaints and objective safety concerns are consistently captured. The participant timeline and assessment schedule are detailed in figure 1.

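### The duty to notify the team of dizziness, paraesthesia, chest discomfort or presyncope is written only for the slow-breathing exercise, so reported counts of these symptoms may be raised in the SDB arms by unequal ascertainment

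*Protocol article*

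**What the plan says.** Four parts of the protocol article bear on this.

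- **Diaphragmatic breathing** (Intervention and comparator): "Safety monitoring will require immediate cessation of the exercise and notification of the study team in cases of dizziness, paraesthesia, thoracic discomfort or presyncope". The sentence sets no threshold of severity or novelty. Nothing similar appears under Auricular vagal neuromodulation therapy or Sham stimulation, and the legend of Figure 1 describes normal breathing (NB) simply as spontaneous breathing.
- **Secondary outcomes, entry on AEs**, for all participants: "Participants will be encouraged to report any new or unusual symptoms to the study team promptly", and "If any severe or concerning symptoms arise, participants will be instructed to contact the study team immediately". The same entry says that "participants might be asked to complete a simple AE questionnaire on a weekly basis".
- **Harms**, also for all participants: "They will be assessed systematically through weekly AE questionnaires, supplemented by spontaneous reports from participants via phone, email or during visits". It continues: "All events will be recorded in the case report form, including their severity, onset and duration".
- **Objectives**: the safety objective covers tolerability and adverse events, "with descriptive comparisons of event profiles across the four groups".

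The Background and the section on screening undiagnosed participants both list dizziness among the characteristic symptoms of POTS. The Background also grants that slow-paced diaphragmatic breathing (SDB) can now and then make a patient light-headed when it is done incorrectly.

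**The concern.** A comparison of adverse events between arms is fair only if each arm has the same chance of having an event noticed and written down. Here two of the four arms have an extra route. A participant in an SDB arm who becomes dizzy during practice must tell the team. A participant in an NB arm with the same familiar dizziness is asked to volunteer it only if it seems new, unusual, severe or concerning, and for many people with POTS it will be none of these.

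At stake is the reading of the safety table. A surplus of dizziness or presyncope in the SDB arms could be taken as harm from slow breathing, or from its combination with stimulation, when part of it reflects who was obliged to report. Because SDB may also cause such symptoms in truth, a real signal and a reporting artefact would fall on the same symptoms in the same arms. A table that pools all sources could not separate them.

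**Working it through.** The protocol gives no adverse event rate and no capture rate, so there is no stated figure to reproduce. The check has two steps: compare the reporting routes, then illustrate the possible size under stated assumptions.

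**Step 1. Reporting routes for one episode of ordinary dizziness**

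| Route (section) | SDB arms | NB arms |
|---|---|---|
| Stop-and-notify (Diaphragmatic breathing) | Required if it occurs during practice | No rule stated |
| Volunteered report (Secondary outcomes, AEs) | If new or unusual | If new or unusual |
| Immediate contact (Secondary outcomes, AEs) | If severe or concerning | If severe or concerning |
| Weekly AE questionnaire (Harms) | Yes | Yes |
| Weekly tolerability questions (Strategies to improve adherence) | Yes | Yes |
| Calls at weeks 2, 6 and 10 (Plans to promote participant retention and follow-up) | Yes | Yes |

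Only the first row differs. Whether it adds anything depends on how much the common rows already capture. The main common row is itself stated in two ways: the AEs entry makes the weekly questionnaire optional, and Harms makes it systematic.

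**Step 2. Illustration of size**

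From the protocol: 25 participants per group, so 50 in the two SDB arms and 50 in the two NB arms.

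Assumed:
- p, the true proportion of participants with such a symptom, is equal in both breathing conditions.
- q is the proportion of affected participants captured by the common collection, the same in all arms.
- s is the proportion captured by the exercise notification, in SDB only, taken as 0.3 to 0.7 and independent of q.

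Formulas:
- NB participants with a report = 50 × p × q
- SDB participants with a report = 50 × p × [1 − (1 − q)(1 − s)]
- Ratio SDB/NB = [1 − (1 − q)(1 − s)] / q, in which p cancels

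Worked example at q = 0.5:
- s = 0.3: [1 − 0.5 × 0.7] / 0.5 = 0.65 / 0.5 = 1.30
- s = 0.7: [1 − 0.5 × 0.3] / 0.5 = 0.85 / 0.5 = 1.70

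All results, with participant counts at p = 0.4 (20 truly affected in each set of 50):

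| q | Ratio, s = 0.3 to 0.7 | NB with a report | SDB with a report |
|---|---|---|---|
| 0.50 | 1.30 to 1.70 | 10.0 | 13.0 to 17.0 |
| 0.80 | 1.075 to 1.175 | 16.0 | 17.2 to 18.8 |
| 0.95 | 1.02 to 1.04 | 19.0 | 19.3 to 19.7 |
| 1.00 | 1.00 | 20.0 | 20.0 |

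The excess shrinks as common capture improves and vanishes when it is complete. It also shrinks as s falls, for example if few of these symptoms arise during the short daily practice.

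The illustration counts participants with at least one report. If every notification were entered as its own event, event counts could still differ between arms at q = 1, because notifications arise by session and the questionnaire by week.

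**The case against.** The strongest reply is that adverse events are mainly collected in a way that does not depend on arm. Harms are assessed by a weekly questionnaire with no filter for novelty. Tolerability is asked about weekly, there are follow-up contacts every 2–3 weeks, and everyone is told to call at once about severe symptoms. An event both notified and captured by questionnaire is one event. This stands: with near-complete common capture the excess is negligible for participants with an event.

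A reader might go further than the text allows in three ways.

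- **That SDB counts are certain to be raised by the rule.** The documents do not show this. The excess can be nil, and a higher count may be a true effect of SDB.
- **That the number of notifications measures the bias.** Twelve weeks of daily practice is 12 × 7 = 84 sessions, and 25 × 84 = 2,100 sessions per SDB arm. At assumed symptom rates of 1%, 2% or 5% of sessions that gives 21, 42 or 105 notifications. These are gross reports under full adherence and no dropout. They are not net excess events, because many may reach the record anyway and some may be genuine SDB effects.
- **That the rule itself is misplaced.** It is a precaution tied to an exercise, and its clinical content is not questioned here. If NB is only spontaneous breathing, there is no exercise to stop.

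Two further replies carry some weight. The article does not describe how NB is delivered, although its blinding section speaks of NB techniques, so the full protocol may hold a matching instruction. Source flags and table layouts are also often left to the case report form or the analysis plan. The finding therefore rests on what the article does state: an arm-specific reporting duty, a common questionnaire described in two incompatible ways, and a comparison across the four groups.

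**Conclusion.** The point holds as a risk of unequal ascertainment. The symptom-specific duty to notify is written only for the SDB exercise, the unsolicited routes common to all arms have a higher threshold, and all recorded events enter a comparison across groups. Reported counts of these four symptoms may therefore be raised in the SDB arms at equal true risk.

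The size is unknown from the documents. The ratios above rest on the assumed q and s and on their independence. They would matter if the weekly questionnaire were optional or poorly completed, and would be negligible if it were given and returned almost without fail. The conflict between the AEs entry and Harms over that questionnaire is thus what decides whether the risk is real in practice.

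The consequence is limited. The comparison is descriptive, no test depends on it, and the primary endpoint is untouched. This is a worthwhile refinement, not a flaw that threatens the trial.

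**What to change.** Leave the stop-and-notify rule unchanged, and then:

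1. Reconcile the AEs entry under Secondary outcomes with Harms, so that the weekly AE questionnaire is definite and given identically in all four arms.
2. Record in the case report form how each event became known (questionnaire, exercise-stop notification, other spontaneous report, visit or call).
3. Base the main four-group comparison of dizziness, paraesthesia, thoracic discomfort and presyncope on the questionnaire, counting participants with an event.
4. Show events known only from exercise-stop notifications separately by arm, next to an all-sources table that includes serious events from every source, so that no event drops out of sight.

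The cost is one extra field and one extra table, plus a sentence in the safety analysis. Under Trial design, enrolment is stated to have begun on 19 March 2026. The field should be added soon, since the source is easy to note when a report arrives and may be hard to reconstruct later.

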#### Criteria for discontinuing or modifying the intervention

Participation in the intervention may be discontinued or modified if participants experience side effects that make continuation unreasonable. Such side effects include local skin irritation at the electrode site, pain or severe discomfort during stimulation, pronounced dizziness, syncope, chest discomfort or nausea. Pregnancy during the study period is also an exclusion criterion. In addition, participants may withdraw from the intervention at any time on request, without disadvantage. All modifications or withdrawals will be systematically documented and included in the analysis.

#### Strategies to improve adherence

Adherence is maintained through a multistep process. At the start of the study, participants receive thorough training from a physiotherapist with over 10 years of clinical experience in respiratory and autonomic therapy. This training covers detailed instructions on correct device use, electrode placement and performing the breathing exercises. During the study, daily usage of AVNT and breathing training is logged via a mobile application that records usage time and frequency. Weekly adherence questionnaires are gathered to document how often, how long and how well the interventions are tolerated. Regular follow-ups (every 2–3 weeks), either by phone or in person, are conducted to help keep motivation high, address concerns and support compliance.

#### Concomitant care

Existing pharmacological treatments for POTS (such as β-blockers, ivabradine, midodrine or fludrocortisone) may be continued throughout the 12-week intervention period, provided that the medication regimen has been stable for at least 4 weeks prior to enrolment. Changes in medication during the intervention phase should be avoided whenever possible. If medication adjustments are medically necessary, these changes will be documented and considered in appropriate subgroup or sensitivity analyses. Concomitant therapies that directly influence autonomic function (eg, additional vagal stimulation methods, newly initiated breathing techniques or newly started autonomic-modulating medications) are not permitted during the intervention period. Supportive non-pharmacological measures, such as increased fluid intake, higher salt consumption or the use of compression garments, are allowed, as they reflect standard care for individuals with POTS.

